#### Relevant concomitant care permitted or prohibited during the trial {11d}

Relevant additional treatments (e.g., individual psychotherapy) administered to the participant upon entry to the trial or at any time during trial participation are regarded as concomitant treatments and will be documented. Concurrent participation in CBT-based skills trainings similar to START NOW disqualifies from participation. Concomitant medication will be recorded.

### Provisions for post-trial care {30}

Not applicable. The study has undergone evaluation by the Ethics Commission Northwestern and Central Switzerland (EKNZ) and has been categorized as having minimal risks and burdens (Risk category A according to ClinO, Article 61). The study does not involve any invasive or clinical data assessment procedures that would cause adverse (psychological) responses.

### Outcomes {12}

#### Primary endpoints

The primary focus is on the post-intervention psychological inflexibility measured by AFQ-Y scores between baseline (T_1_) and follow-up (T_3_) (12 weeks +/− 2 weeks after end of intervention). The AFQ-Y is a validated self-rating questionnaire assessing PF in adolescents and young adults. Items are based on ACT models of human suffering representing the theoretical concept of psychological inflexibility due to high cognitive fusion and experiential avoidance [37]. Participants answer 17 items indicating how true each item is for them on a 5-point Likert scale (0 = not at all true; 4 = very true). Higher total scores indicate lower PF. Data will be assessed within 2 weeks before start of skills training (baseline, T_1_), within 2 weeks after end of skills training (T_2_), as well as at 12 weeks (+/− 2 weeks) (T_3_) and 24 weeks (+/− 2 weeks) (T_4_) post skills training. Primary endpoint is the change in total score between baseline (T_1_) and follow-up (T_3_). Total scores can range between 0 and 68. Accordingly, a change in score can range between − 68 and + 68.

Further objectives of the current trial are to assess the effect of treatment (immediately after the end of intervention) on other psychological health-related outcome measures (i.e., general resilience, psychological well-being, self-efficacy, general impairment, anger-irritability, training substance use) in participants of the three conditions. Furthermore, resilience will also be assessed for caretakers.

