### Trial design {8}

The study is a monocentric, prospective, confirmatory randomized controlled trial with three experimental conditions: (1) START NOW as web-based group training guided by a facilitator, (2) START NOW as web-based pure self-help training, and (3) TAU. Institutions are randomly assigned 2 weeks before the 9-week intervention phase.

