**Fig. 1 Fig1:**
[figure not shown]
Trial schedule *Note. T*_*1*_,* T*_*2*_,* T*_*3*_,* T*_*4*_ time points; *AFQ-Y* Avoidance and Fusion Questionnaire for Youth; *MAYSI-2* Massachusetts Youth Screening Instrument-2; *CD-RISC* Connor-Davidson Resilience Scale; *WHO-5* World Health Organization – Five Well-Being Index; *CIS* Columbia Impairment Scale; *PHQ-4* Patient Health Questionnaire-4; *SWE* Skala zur Allgemeinen Selbstwirksamkeitserwartung [General Self-Efficacy Expectancy Scale]; *CSQ* Client Satisfaction Questionnaire; *ARI* Affective Reactivity Index; *EssenCES* Essen Climate Evaluation Schema; *TSQ* Trainer Satisfaction Questionnaire*.* Data will be collected at screening (T_0_), ≤ 4 (+ 2) weeks before the intervention (T_1_; baseline assessment), ≤ 2 weeks after the intervention has ended (T_2_; post-intervention assessment), 12 ± 2 weeks post intervention (T_3_; first follow-up), and 24 ± 2 weeks post intervention (T_4_; second follow-up)

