### Assignment of interventions: blinding {17}

#### Who will be blinded {17a}

Not applicable. After randomization, the START NOW study team will inform the participating institution, and consequently, the participants, about their allocation to the respective condition.

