### Statistical methods {20}

#### Statistical methods for primary and secondary outcomes {20a}

A detailed statistical analysis plan will be written by the study statistician and kept under version control at the DCR. The statistical analysis plan will be finalized before the last visit of the last patient and the final version will be stored before access to the study database is granted.

All outcomes of interest will be described stratified by intervention group at each of the time-points of assessment by mean and standard deviation, median, or median and interquartile range, as appropriate. We will also visualize the time course of the endpoints of interest by intervention group.

The primary objective is to compare the follow-up AFQ-Y score (12 ± weeks after the end of the intervention) between the 3 intervention arms. To this end, we will perform an intention-to-treat analysis, analyzing all participants in the groups they were randomized to, regardless if they actually completed the particular intervention. We will use the imputed full analysis set for the primary analysis. The primary endpoint is the change in AFQ-Y score from baseline (T_1_) to the first post intervention follow-up (T_3_, 12 ± weeks). We will fit a linear mixed-effects model for the primary endpoint post intervention AFQ-Y score. The identifier of the institution group will be included as a random intercept to account for the clustered data structure (i.e., participants in training groups within institutions). The intervention (3 levels with TAU as reference) will be included as a fixed effect of interest, and the baseline AFQ-Y score is included in the model as a covariate. We will examine the distribution of the residuals to assess the model assumptions. The estimate of the fixed effect will be presented together with the corresponding 95% confidence interval and p-value. All analyses will be performed in R version 4.3.1 or higher.

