#### Methods in analysis to handle protocol non-adherence and any statistical methods to handle missing data {20c}

The primary analysis will be conducted using the full, imputed analysis set comprising all eligible participants with baseline measures of the focal endpoint and according to the intention-to-treat principles. We also define the per-protocol analysis set comprising all eligible participants with a baseline measure for the focal endpoint and considered compliers according to the definition above.

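### The two T1 windows conflict, one puts the baseline AFQ-Y at or after randomisation, and the full analysis set is limited to participants with that baseline despite the intention-to-treat statement

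*Protocol article*

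**What the plan says.** **Timing of T1.** The Primary endpoints section of the protocol article states: "Data will be assessed within 2 weeks before start of skills training". The note to Fig. 1 gives a longer window for the same assessment: up to "4 (+ 2) weeks before the intervention".

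**Timing of randomisation.** Trial design {8}: "Institutions are randomly assigned 2 weeks before the 9-week intervention phase". Sequence generation {16a} and Implementation {16c} make consent and passed screening of at least four participants the trigger. Neither mentions T1.

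**Disclosure.** Concealment mechanism {16b} reveals the allocation to the study team through REDCap once randomisation is done. Section {17a} continues: "After randomization, the START NOW study team will inform the participating institution, and consequently, the participants, about their allocation to the respective condition". No date is set for telling participants, and disclosure is not tied to completion of T1.

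**Use of T1.** The AFQ-Y is a self-rating. The primary endpoint is its change from T1 to T3. Section {20a} fits a linear mixed model to the follow-up score with the baseline score as covariate.

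**Who is analysed.** Section {20a} promises an intention-to-treat analysis, "analyzing all participants in the groups they were randomized to". Section {20c} restricts the primary analysis to the "full, imputed analysis set comprising all eligible participants with baseline measures of the focal endpoint". Multiple imputation is described for missing outcome values, with baseline values named only as predictors.

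**The concern.** A baseline covariate in a randomised comparison should not be open to influence by the allocation. Here it is a questionnaire answered by unblinded young people, and one of the two stated windows begins no earlier than randomisation. If knowing the arm changes how some of them answer, the adjustment carries part of that change into the treatment contrast.

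The analysis set is a second, separate route. If T1 can follow disclosure, having a T1 value is a post-allocation event. A set restricted to participants with T1 then leaves out some who were randomised, and whether they are left out may depend on arm. That is not the analysis promised in {20a}. As written, a missing T1 is not rescued by the imputation.

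Both routes lead to the primary result: one through the covariate, the other through the denominator.

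**Working it through.** **1. Timeline (week 0 = start of training)**

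| Event | Week | Source |
|---|---|---|
| Randomisation | −2 | Trial design {8} |
| Team informed | on randomisation | {16b} |
| Institutions, then participants informed | after randomisation, no date | {16b}, {17a} |
| T1, first statement | −2 to 0 | Primary endpoints |
| T1, second statement | −4 (or −6) to 0 | Fig. 1 note |

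Under the first statement no part of the T1 window precedes randomisation. Under the second, T1 may fall on either side. Nothing requires T1 to come first.

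**2. Inputs for the size**

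- From Sample size {14}: mean 21.04, SD 13.01, correlation between time-points 0.80, planned d = −0.50 (self-help) and −0.80 (group), effective 26 per arm.
- From Table 1: AFQ-Y ≥ 34.05.
- Assumed here: a shift in T1 in one arm of 0.05, 0.10 or 0.20 SD (0.65, 1.30 or 2.60 points), because the documents give none; the 0.80 correlation also holding between T0 and the later scores; two-sided 5% tests.

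The plan states no figure on this point. Its sample size is not in dispute and reproduces from these inputs: 78 × [1 + (4 − 1) × 0.2] × 1.2 = 149.8, so 150.

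**3. Slope of T3 on T1**

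Bias of the adjusted contrast (absolute size) = slope × shift. Without selection the slope is 0.80.

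The cut-off lies exactly one SD above the planning mean: (34.05 − 21.04)/13.01 = 1.00. In units of 13.01²:

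- λ = φ(1)/[1 − Φ(1)] = 1.525
- Var(T0 | selected) = 1 + 1.525 − 1.525² = 0.199
- Var(T1) = 0.64 × 0.199 + 0.36 = 0.487
- Cov(T1, T3) = 0.64 × 0.199 + (0.80 − 0.64) = 0.287
- slope = 0.287/0.487 = 0.59

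**4. Bias of the adjusted contrast**

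| Assumed shift | Slope 0.59 | Share of d = 0.50 (6.5 points) | Slope 0.80 | Share of d = 0.50 |
|---|---|---|---|---|
| 0 | 0 | 0 | 0 | 0 |
| 0.05 SD | 0.38 points | 6% | 0.52 points | 8% |
| 0.10 SD | 0.77 points | 12% | 1.04 points | 16% |
| 0.20 SD | 1.53 points | 24% | 2.08 points | 32% |

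For the type I error, take SE = residual SD × √(2/26). The residual variance of T3 given T1 is 0.487 − 0.287²/0.487 = 0.318 with selection and 1 − 0.80² = 0.36 without. The SE is then 2.03 or 2.16 points. A 0.20 SD shift raises the two-sided 5% error to about 0.12 or 0.16. Simulation without selection gave 0.154 at 0.20 SD; with no shift it gave a bias of 0.000 SD and an error of 0.0495.

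**5. Selective absence of T1**

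Suppose a share m of one arm lacks T1, and absence is governed by a variable with correlation c to the T3 residual. Then bias = 0.6 × c × φ(k)/(1 − m) × 13.01, where k is the upper m-quantile of the standard normal. With m = 5% and c = 0.2: 0.6 × 0.2 × 0.109 × 13.01 = 0.17 points. With m = 20% and c = 0.5: 0.6 × 0.5 × 0.350 × 13.01 = 1.37 points. Both m and c are assumed.

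**6. Precision if T0 replaces T1 as covariate**

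Residual variance of T3 is 0.36 given T0 and 0.318 given T1. The ratio is 1.13, so about 13% more variance, or a standard error √1.13 = 1.06 times as large.

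**The case against.** **Timing is a possibility, not an event.** A reader might infer that T1 was collected after participants knew their arm. The documents do not support that. The Fig. 1 window allows T1 before randomisation, no disclosure date is given, and no T1 dates are reported. This limits the claim about bias; it does not remove the conflict between the windows.

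**A covariate taken after randomisation is not biased in itself.** Bias arises only if knowing the arm changes the T1 answers or who gives them. This stands.

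**The size is easily overstated.** Taking r = 0.80 and a 0.20 SD shift, a reader might say that a third of the smaller planned effect is at risk. The trial enrols only those at or above the cut-off, and under the planning model the slope there is 0.59. The same shift gives about a quarter. Nor would the full 2.6 points pass through: that describes an unadjusted change-score test, and the planned model adjusts for baseline.

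**There are safeguards.** Vouchers and reminders apply in all arms, CHF 20 is deducted for each missed time-point, TAU participants receive the WebApp later, and randomisation follows consent and screening. Arm-dependent non-response at T1, such as by disappointed TAU participants, is therefore conjecture. The number without T1 is not given.

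**Requiring a baseline is a familiar modified intention-to-treat rule.** True, but the article presents it as intention-to-treat without qualification, and the two descriptions do not define the same set.

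**Conclusion.** Two defects stand on the text alone. The T1 windows in the Primary endpoints section and the Fig. 1 note disagree. The full analysis set in {20c} is narrower than the population promised in {20a}. Together with randomisation 2 weeks before the start and no blinding, the first window puts the covariate of the primary model, and entry to its analysis set, at or after randomisation.

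The consequence is a risk of unknown size. For an assumed shift of 0.05 to 0.20 SD in one arm, the adjusted contrast is biased by about 0.4 to 1.5 points under selection at the cut-off, or 0.5 to 2.1 points with the unselected correlation; with no shift, by nothing. The direction depends on which arm shifts and which way. The lower range assumes the planning distribution, a 0.80 correlation that extends to T0, and the AFQ-Y cut-off applied to everyone.

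Confidence is high in the inconsistencies and much lower in any particular size. A reader might conclude that T1 must be replaced as the primary baseline. The documents do not carry that far: the primary endpoint is defined from T1, recruitment has closed, and harm from T1 is not shown.

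**What to change.** 1. **Reconcile the T1 windows** and state the order of T1, randomisation and disclosure that was actually followed.
2. **Define the full analysis set as all randomised participants.** Extend the multiple imputation to a missing T1, with the T0 AFQ-Y in the imputation model. Because the AFQ-Y is an inclusion criterion and screening precedes randomisation, a T0 score exists for everyone randomised. This removes arm-dependent exclusion.
3. **Prespecify a sensitivity analysis** that repeats the primary model with T0 AFQ-Y in place of T1. T0 cannot be affected by the allocation.
4. **Report by arm** the number without T1 and the T1 date relative to the randomisation date. A rule based on the date when participants were told is not workable from the documents, which do not say that this date is recorded.

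**Cost.** No new data and no change to the sample size of 150. The set definition and the sensitivity analysis belong in the statistical analysis plan, which {20a} says is finalised before the last participant's last visit; any protocol amendment also goes to the ethics committee. The T0-adjusted model carries about 13% more residual variance under the planning assumptions. Keeping T1 in the primary model leaves the stated endpoint as it is.

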#### Secondary endpoints

Change will be assessed at baseline (T_1_) and (i) post skills training (T_2_), (ii) 12-week follow-up (T_3_), and (iii) 24-week follow-up (T_4_).Resilience: *Connor-Davidson Resilience Scale* (CD-RISC) [41] Self-reported psychological well-being: *World Health Organization - Five Well-Being Index* (WHO-5) [42] in self-rating by participantSelf-reported self-efficacy: total score on the German *Skala zur Allgemeinen Selbstwirksamkeitserwartung* [*General Self-Efficacy Scale]* (SWE) [43] in self-rating by participantGeneral impairment: all sub-scores and total score on the *Columbia Impairment Scale* (CIS) [44] both in self-rating by participant and external rating by caretakerDepression and anxiety: total score on the *Patient Health Questionnaire-4* (PHQ-4) [45, 46] in self-rating by participantsAnger-irritability: total score on *Affective Reactivity Scale* (ARI) [47] both in self-rating by participant and external rating by caretakerSubstance use: total score on the Alcohol/Drug Use subscale of the *Massachusetts Youth Screening Instrument-2* (MAYSI-2) [48] in self-rating by participants

##### Resilience

General resilience will be measured by the *Connor-Davidson Resilience Scale* (CD-RISC) in the 10-item version [49]. It refers to an individual’s ability to endure difficult experiences. This scale consists of 15 items on a 5-point Likert scale ranging from 1 (strongly disagree) to 5 (strongly agree). Total scores can range from 0 to 50, with change scores ranging from − 50 to +50.

##### Well-being

Psychological well-being will be assessed by *The World Health Organisation- Five Well-Being Index* (WHO-5) [42]. The self-report questionnaire contains five items on a 6-point Likert scale ranging from 5 (*all of the time)* to 0 *(none of the time*). Respondents are asked to indicate how often they felt well during the last 2 weeks. Total scores can range from 0 to 25, with higher scores indicating greater well-being. Accordingly, change scores range from − 25 to +25.

##### Self-efficacy

Self-efficacy will be assessed by the German self-report questionnaire *Skala zur Allgemeinen Selbstwirksamkeitserwartung [General Self-Efficacy Scale]* (SWE) [43]. The questionnaire includes 10 items and a 4-point Likert scale ranging from 1 *(not true) to 4 (completely true*). The scale reflects one’s convictions on subjective controllability or competence expectations in different demanding situations, with higher scores indicating a greater sense of self-efficacy. Total scores can range from 10 to 40, with change scores ranging from − 30 to +30.

##### General impairment

General impairment will be assessed by the *Columbia Impairment Scale* (CIS) [44]. The 13-item questionnaire captures functional impairment in four domains: interpersonal relations, broad psychopathological domains, functioning in school or at work, and use of leisure time. It will be answered both by the participant as a self-report questionnaire, and by the caretakers as external raters. Items are answered on a 5-point Likert scale ranging from 0 (*no problem) to* 4 (a *very big problem*). Total score can range from 0 to 52, with change scores ranging from − 52 to +52.

##### Depression and anxiety symptoms

The Patient Health Questionnaire-4 (PHQ-4) is a short questionnaire with two sub-scales (depression and anxiety). The PHQ-4 is a reliable, valid, and precise screening tool for self-reported depression, anxiety, and general psychological distress [45, 46, 50]. Answers are given on a 4-point Likert scale ranging from 0 (not at all) to 3 (nearly every day). The sum of all items comprises the total score. Total scores are rated categorized as normal (0 to 2), mild (3 to 5), moderate (6 to 8), and severe (9 to 12). A score ≥ 3 for items 1 and 2 suggests anxiety. A score ≥ 3 for items 3 and 4 suggests depression.

##### Anger-irritability

Reactivity will be measured by the *Affective Reactivity Index* (ARI) [47]. It will be answered by AYA youth as self-report questionnaire and by caregivers as external raters to indicate irritable mood. It contains seven items to be scored on a 3-point Likert scale ranging from 0 (*not true) to 2 (certainly true*). The total score is calculated as the sum of items 1 to 6, resulting in a range from 0 to 12. Item 7 addresses the perceived degree of suffering and is analyzed separately.

##### Substance use

Within the screening for eligibility, signs of mental/emotional disturbance, such as alcohol and drug use, will be assessed using the *Massachusetts Youth Screening Instrument-2* [48]. It is a brief screening tool designed for adolescents between the ages of 12 to 17 years. The MAISY-2 contains 52 items across seven subscales: alcohol/drug use, anger-irritability, depression-anxiety, somatic complaints, suicide ideation, traumatic experiences, and thought disturbance. Respondents are asked about the presence of various thoughts, feelings or behaviors in the past few months, in a *yes* or *no* format. Each subscale contains different caution cut-offs.

##### Client training satisfaction

Participants within the two intervention conditions can indicate their satisfaction with the training using the *Client Satisfaction Questionnaire* (CSQ) [51] at T_2_ (post intervention). The CSQ was specifically developed to assess participants’ experiences and satisfaction with START NOW. This scale consists of 8 items on a 4-point Likert scale ranging from 0 to 3 and two open questions about what participants liked or would want to be changed within the training. Total scores can range from 0 to 24.

##### Trainer satisfaction

Satisfaction of facilitators within the guided group training condition will be assessed with the *Trainer Satisfaction Questionnaire* (TSQ) [51] at T_2_ (post intervention), a 5-min self-rating questionnaire. After the conclusion of the second follow-up (T_4_), individual semi-structured expert interviews are planned for all interested institutions, whether they participated in the study or were unable to do so (minimum of two individually interviewed employees per institution). The interviews will last 45–60 min and cover topics such as reach, effectiveness, adoption, implementation, and maintenance of intervention programs, including START NOW.

##### Social atmosphere

Social atmosphere will be assessed with the German version of the *Essen Climate Evaluation Schema* (EssenCes) [52]. It is a short self-rating questionnaire, containing 17 items across three subscales: therapeutic hold, patients’ cohesion and mutual support, and experienced safety. Responses are given on a 5-point Likert scale ranging from 0 (*not at all)* to 4 *(very much*). Total scores can range from 0 to 68 with higher scores indicating a better social climate.

##### Checklist baseline T_1_ and checklist monitoring

Inclusion/exclusion criteria throughout the study (i.e., participation in concurrent CBT-based skills training similar to START NOW., internet access, external placements/discharge, unauthorized leaves) will be screened/monitored with two checklists specially designed for this purpose.

##### Prior experiences of caretakers and facilitators

The professional qualification of involved caretakers and facilitators and their experiences with START NOW or other forms of resilience trainings will be assessed with a short questionnaire. For caretakers, the assessment is at baseline (T_1_), for facilitators, professional qualification is assessed post-intervention (T_2_).

##### Adherence

For each institution, the quality of the group training guided by a facilitator will be rated by a START NOW facilitator during the second session (either live or via online connection) using a *Quality Assurance Form* [40]. Furthermore, participant adherence will be recorded through a) attendance lists created by caregivers in the group condition and b) usage logs of the WebApp, specifically finished sessions.

